### Participants

We randomly selected 14 research sites from among all community mental health clinics (CMHCs) in Delaware and Connecticut. These agencies serve approximately 8,000 consumers. We used the Power and Precision software package (Biostat, Englewood, NJ, USA) to calculate sample sizes needed to achieve 80% power (α = 0.05) to detect these effects in our two-level hierarchical design where clinicians and patients are nested within CMHCs. The software accounts for this nesting using the intracluster correlation coefficient (ICC), a measure of the relatedness of clustered data that compares the variance within and between clusters. The ICC in our pilot data was 0.013. To achieve the study aims, we will need 280 participants (20 per site). We will need 1,125 medical record reviews (75 per site).

The services delivered at the CMHCs include psychiatric crisis intervention, individual and group therapy, psychiatric evaluation, medication management, case management, community support programs and rehabilitation services. A total of 280 providers will be recruited for the study. Within each research site, five clinical supervisors, ten direct care staff and five leadership staff will be recruited to participate in the study. The supervisors are clinical staff who are directly responsible for supervising the direct care staff. Direct care staff are clinicians who provide frontline services to consumers without any supervisory duties. The supervisors and direct care staff work in the outpatient mental health programs listed above. They come from a variety of disciplines, including social work, psychology, psychiatric rehabilitation, counseling and peer support. The leadership staff are in administrative positions and do not directly supervise direct care staff. Their titles include executive director, medical director, administration direction, operations director, quality improvement director, clinical services directors, peer support or consumer affairs director, training and staff development director, rehabilitation services director, human resources director, and representatives from the agency’s consumer advisory council.

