### Randomization

The 14 sites (8 in Connecticut and 6 in Delaware) selected for the study will be randomized into the 2 study arms, yielding 7 sites per condition, balanced by state. A research team member will use SAS 9.3 software to generate the allocation sequence assigning sites to condition. The software will generate randomized lists blocked by state, ensuring three experimental sites and three control sites in Delaware and four experimental sites and four control sites in Connecticut. The responsible team member will be blinded to site-specific information during randomization. Blinding is not possible, given the circumstances of the intervention.

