### Measurement

The intervention will be conducted over a period of 12 months and will be staggered across experimental sites. Organizational factors and PCCP competency will be measured by surveys of the leaders, clinical supervisors and direct care staff because reliable assessment requires multiple perspectives [30]. These surveys will be administered at baseline, 6 months and 12 months. Chart reviews will also be used to measure PCCP competency. Service engagement and consumer outcomes will be measured using state mental health data and Medicaid claims data.

Online assessment measures will be administered to all study participants, regardless of treatment condition. Researchers will collaborate with each CMHC to identify the leadership staff, clinical supervisors and direct care staff. An e-mail with an embedded URL linking participants to the online consent form and survey will be sent to each provider individually. Depending on their role in the agency, staff will receive one of the three surveys for direct care staff, clinical supervisors or executive leadership. The surveys are substantively equal with variation in the measurement versions and included language. Surveys will be completed at three time points: baseline, the midpoint of the intervention period (6 months) and postintervention (12 months). Each research site in the control condition will be paired with a site in the experimental condition, and the surveys will be e-mailed to pairs 1 month prior to the experimental site’s receipt of the PCCP intervention. Chart reviews will assess 75 service plans per site before and after the intervention.

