### Quantitative Data analysis

All analyses will be done by intent to treat (ITT). Differences across the two arms of the study (PCCP and treatment as usual) will be analyzed using the PROC MIXED statement in SAS statistical software (SAS Institute, Cary, NC, USA) to create mixed-effects multivariate regression models. Mixed-effects models will permit the appropriate analysis of nesting of study subjects within sites and repeated measurement of outcomes for subjects over time. Descriptive statistics will be examined for treatment groups and for additional groups as needed (for example, treatment completers versus dropouts). In addition, individual and average trajectories will be plotted for all repeated measures over time according to assigned treatment.

Bivariate analyses will be conducted using *χ*^2^ tests for categorical variables and *t*-tests for continuous dependent variables at each time point to evaluate the differential impact of the PCCP intervention on each consumer and implementation outcome. All models will control for, as fixed effects, baseline consumer factors as appropriate (diagnosis, comorbid medical and substance abuse diagnoses, sex, age, race and psychiatric hospitalization rates). Models will be conducted separately for outcomes from leadership staff, clinical supervisors, chart reviews, state mental health data and Medicaid claims. The unit of observation in all models will be, as appropriate, clinical supervisors, organizational leaders or consumers.

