The analyses for aim 2 are limited to only clinicians and consumers in agencies exposed to the intervention. Within this population, we will use linear mixed-effects regression models to determine the extent to which clinician assessments of organizational factors, including transformational leadership, recovery orientation and organizational readiness (independent variables), are associated with our primary implementation outcome, which is clinician PCCP competency (dependent variable). Competency will be measured as change from baseline to 12 and 24 months and examined separately at each time point. Our first model will include one observation per clinician and will include a random intercept for organization, but no independent variables. This will allow us to calculate the maximum proportion of variance attributable to the organization (that is, the ICC). A second model will also include our three independent variables as fixed effects. This model will allow us to examine the individual contribution of each organizational factor to explaining competency and also to understand how much of the total explainable organizational variation in our dependent variable from the first model is explained by the three organizational factors in this model. In subsequent models, we will use these same techniques to assess the impact of organizational factors on patient outcomes, including consumer satisfaction with services, service engagement and adherence and consumer clinical and functional status.

Aim 3 is to use qualitative methods to understand how care planning impacts service engagement and how implementation processes influence organization and provider level behavior.

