## Conclusions

Designed to bridge the science to services gap, this study is focused on how agencies can bring about the wholesale transformation needed to deliver sustainable person-centered care. The PCCP intervention is designed to address a pressing public health problem—the high rates of disengagement from public mental health services. The aim is to generate valuable guidance on how state systems engaged in the transformation process can best use their limited resources during times of significant fiscal constraint. The study has support from both state policy makers and individual agencies, meaning that that the findings will likely inform future policies and practice. PCCP has the potential to enhance the impact of all EBPs and recovery-oriented practices and bring practice in line with national guidelines that have emerged as a result of health care reform.

By focusing on training supervisors in addition to direct care staff, the study can increase its external validity and build CMHC internal capacity. Training supervisors based upon our experience of conducting statewide training is the most efficient and feasible way to promote agency-wide transformation. We can considerably extend the reach of PCCP with this strategy, allowing for large-scale replication implemented at the state level. Also, training supervisors increases the sustainability of PCCP by building internal skills and capacity among a more stable clinical leadership group, as opposed to focusing efforts on a direct service provider group, which tends to suffer from high rates of turnover within public sector mental health systems. The study addresses implementation by measuring organizational factors to assess both whether the intervention is effective and under what conditions it is effective. In addition, in the qualitative inquiry, we will examine the implementation process from the perspective of multiple stakeholders. By paying attention to organizational factors, we aim to inform the next step in PCCP research, which is to design and test implementation strategies to ensure the successful adoption of PCCP in real-world settings.

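### Aim 2 uses only the 7 intervention agencies, so it cannot show under what conditions PCCP is effective, and its share of organizational variance explained is close to uninformative

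*Protocol article*

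**What the plan says.** All references are to the protocol article.

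- **Population for Aim 2** (Quantitative Data analysis): "The analyses for aim 2 are limited to only clinicians and consumers in agencies exposed to the intervention". Randomization gives the number of sites: "yielding 7 sites per condition, balanced by state".
- **Models for Aim 2** (same section): a linear mixed model for change in clinician PCCP competency. It is fitted first with only a random intercept for organization. Transformational leadership, recovery orientation and organizational readiness, as assessed by clinicians, are then added as fixed effects. One planned result is "how much of the total explainable organizational variation in our dependent variable from the first model is explained by the three organizational factors". The same techniques are then carried over to satisfaction, engagement, adherence, and clinical and functional status.
- **Purpose**: the opening of Methods defines Aim 2 as covering organizational factors in both the implementation and the effectiveness of PCCP. The Conclusions say the factors are measured "to assess both whether the intervention is effective and under what conditions it is effective".
- **Data in control sites** (Measurement): "Online assessment measures will be administered to all study participants, regardless of treatment condition". The first Participants section plans to use Medicaid and state data for all eligible consumers of the study clinics.
- **Interaction terms**: Aim 1 has a time by treatment term. Neither Aim 1 nor Aim 2 has an arm by organizational-factor term.

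**The concern.** To say under what conditions an intervention is effective is to say that the difference between intervention and control varies with a factor. An analysis without controls does not contain that difference.

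Clinics with stronger leadership or greater readiness may keep consumers engaged, adherent or satisfied whether or not they adopt PCCP. In the 7 treated agencies, such a background link looks the same as a larger PCCP effect in well-led agencies. Survey competency has a further problem: the same staff rate both the organization and its care planning, so part of any association may be a rater effect. Control sites answer the same surveys and could supply the reference, but the plan sets them aside.

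A positive Aim 2 result could therefore reach state systems as advice that PCCP works where leadership is good, when the same link might hold without it. The planned variance-explained figure could strengthen that message although 7 organizations can hardly support it.

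**Working it through.** **Plan's own figure.** The article gives no power or precision figure for Aim 2. Its staff total reproduces: 14 sites × 20 = 280. Each site contributes "five clinical supervisors, ten direct care staff and five leadership staff will be recruited", so Aim 2 has 7 × 20 = 140 staff, or 7 × 15 = 105 without leadership.

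**1. What a treated-only model can identify.** For a site-level factor Z, write the expected outcome as a + b·arm + c·Z + d·(arm × Z). Effect modification is d. In control sites the slope on Z is c; in intervention sites it is c + d. Data from intervention sites alone estimate only the sum c + d. They cannot tell c = 0 with d > 0 from c > 0 with d = 0. With both arms, d is the difference between the two slopes.

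**2. Site-level degrees of freedom** (assuming the factors act at site level).
- Planned model: 7 sites − 1 intercept − 3 factors = 3. The critical two-sided 5% t is 3.18, so a factor needs a partial |r| of 3.18/√(3.18² + 3) = 0.88.
- 14-site model with one factor: 14 − 5 (intercept, arm, state, factor, arm × factor) = 9. The critical t is 2.26, so partial |r| = 2.26/√(2.26² + 9) = 0.60.
- One factor at 7 sites: 7 − 2 = 5. Part of the gain therefore comes from using fewer factors, not from adding controls.

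**3. Chance that the first model finds no organizational variance.** Assume the pilot ICC of 0.013 applies to competency change. The variance estimate is zero when the between/within mean-square ratio is below 1. That has probability P(F < 1/[1 + m·ICC/(1 − ICC)]) with 6 and 7(m − 1) df.
- m = 15: 1 + 15 × 0.013/0.987 = 1.198; P(F(6, 98) < 0.835) = 0.454.
- m = 20: 1 + 20 × 0.013/0.987 = 1.263; P(F(6, 133) < 0.791) = 0.422.
- Simulated REML fits agree: 46% and 41%.
- With 14 sites the probabilities are still 0.377 and 0.331, so doubling the sites does not rescue the statistic.

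**4. Share explained when the factors are pure noise.** The planned quantity is 1 − (organization variance in model 2)/(organization variance in model 1). It was simulated with 7 sites, 15 or 20 staff per site and no true association. Fits with a zero model 1 variance were excluded, because the share is then undefined.

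| Factors | ICC range | Estimation | Share explained by chance |
|---|---|---|---|
| Site-level | 0.013 to 0.30 | REML | median about 0; negative in about half of fits; 50% or more in 24% to 39% |
| Site-level | 0.013 to 0.30 | ML | mean 0.59 to 0.88 |
| Varying between clinicians | 0.05 to 0.30 (assumed) | REML | median about 0 |
| Varying between clinicians | 0.05 to 0.30 (assumed) | ML | median 0.01 to 0.22 |

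The article names PROC MIXED but not REML or ML, and does not say whether clinician ratings are averaged to site level. The chance value depends on both choices.

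**The case against.** **The treated-only model answers a legitimate question.** The stated primary question of Aim 2 is whether organizational factors are associated with clinician competency, which the article defines partly as fidelity to PCCP. Asking which trained agencies implemented better needs no control arm. This stands for the competency model. It does not extend to effectiveness or to the consumer-outcome models. A reader might infer that the whole of Aim 2 is invalid; the article does not support that.

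**The shared-rater problem is mitigated.** Competency is analysed as change from baseline, which removes stable rater differences, and chart review gives a measure that does not depend on survey ratings. This stands in part, so the shared rater is a secondary concern.

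**Low power is acknowledged.** The Mixed methods section concedes it for implementation outcomes and brings in qualitative data. But lack of power is not confounding, and the qualitative work is confined to the experimental sites, so it supplies no control reference.

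**The figures are conditional.** The 3 degrees of freedom assume site-level factors, and the article does not say that the ratings will be aggregated. It also does not name the outcome behind the pilot ICC. Both conditions are carried into the verdict.

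**A stronger reading about chance.** A reader might infer that noise factors would explain 50% of organizational variance on average. That is the null mean of R² for ordinary least squares on 7 site means: 3/(7 − 1) = 0.50. The plan instead compares variance components from mixed models, so the 50% figure should not be stated for it.

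**Conclusion.** The concern holds in a limited form. The article limits Aim 2 to 7 treated agencies and specifies no arm by factor term, yet describes the aim as bearing on effectiveness and on the conditions for it. A treated-only association cannot answer that, whatever the sample size. The mismatch affects the effectiveness wording and the consumer-outcome models. The competency model stands as an implementation analysis within exposed agencies.

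The planned share of organizational variation explained is close to uninformative with 7 sites and three factors. If the factors act at site level, 3 residual degrees of freedom remain. If an ICC of 0.013 applies to competency change, the share is undefined in about 42% to 45% of repetitions. Its chance level otherwise depends on choices the article does not state.

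The change should be made, but it does not affect the Aim 1 comparison of the two arms.

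**What to change.** 1. For the effectiveness and consumer-outcome questions, and for survey or chart competency where it is measured in both arms, add a model on all 14 sites. Include arm, the baseline site-level factor, arm × factor, state, baseline outcome and a site random intercept. Enter one factor at a time, which leaves about 9 site-level degrees of freedom. Report the interaction with its confidence interval and label it exploratory.
2. Keep the treated-only models as a descriptive analysis of implementation in exposed agencies.
3. Do not report the proportion of organizational variance explained as a result.
4. If the 14-site model is not added, remove the statement that the study will show the conditions under which PCCP is effective, and limit Aim 2 to implementation.

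**Cost.** A change of wording and a little more analysis. The surveys and consumer data are already planned in both arms. The interaction intervals will be wide: even with 14 sites, a partial |r| of about 0.60 is needed for significance at the 5% level. A null interaction should therefore not be read as evidence that organizational conditions do not matter.

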**Figure 1 Fig1:**
[figure not shown]
Causal model of person-centered care planning (PCCP).

Transformational leadership is a key upstream organizational factor in creating mental health service organizations that are open to change [22], can improve client outcomes [23] and are recovery-oriented [24]. The leadership qualities that promote transformation are those that inspire providers to adopt the values and goals of their leaders [25]. As opposed to focusing on the completion of specific tasks (transactional leadership), transformational leaders motivate providers by conveying a shared sense of mission and heightening expectations for performance. Recovery orientation is the specific values–innovations fit [26] needed to successfully implement PCCP. Moving toward genuinely person-centered care involves not simply technical skills but also a paradigm shift in how providers understand and value their work with consumers. Nine principles have been identified with regard to recovery orientation, including renewing hope and commitment and redefining self and assuming control [27]. Organizational readiness, which captures both motivation and capacity for change, is now recognized as a critical precursor to successful adoption of innovation in behavioral health care settings [28]. This multifaceted construct reflects how the sum of individual attitudes and behaviors operate at a collective level within an organization [29]. First, staff must be motivated to change by a perceived need for new skills and have confidence in their own ability to adapt to, master and share new skills. Second, organizational climates conducive to change must convey a clear sense of mission and goals, promote staff cohesion and cooperation, and reflect an openness to change. Third, change must be supported by the necessary resources, which include adequate staffing, training, equipment and alignment of procedures [30].

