Trainees will be given the provider training manual as well as a consumer toolkit*.* The provider manual is a published 154-page guide developed by the Yale Program for Recovery and Community Health. The consumer toolkit, also developed by Yale Program for Recovery and Community Health, is a 24-page guide designed to explain to consumers the process of person-centered care planning. Designed for administrators and providers, the manual gives detailed step-by-step guidance on how to write person-centered plans for people receiving behavioral health plans. To strengthen the transfer of learning from the initial training to participants’ daily work, clinical supervisors will be asked to participate in two follow-up TA telephone calls per month. The first call of each month will be a case presentation and consultation call. The supervisor’s team will be invited to participate in the call, and training consultants will offer live modeling of how supervisors should conduct these PCCP feedback sessions with their supervisees. The second monthly call will involve the clinical supervisors only and will be fully dedicated to supporting supervisors with implementation issues they encounter as they encourage the adoption of PCCP by their team members. The training team will keep logs of the training and record process notes of TA calls to measure the frequency and intensity of training given to each provider.

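### The Aim 2 competency model uses each clinician's own rating as an organizational factor, so unless ratings cluster very strongly by site its coefficient mainly reflects disagreement between colleagues at the same agency

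*Protocol article*

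**What the plan says.** The model is in the Aim 2 text of the protocol article, section Quantitative Data analysis. Its scope is set first: "The analyses for aim 2 are limited to only clinicians and consumers in agencies exposed to the intervention". The independent variables are clinicians' assessments of transformational leadership, recovery orientation and organizational readiness. The dependent variable is change in clinician competency in person-centered care planning.

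The layout is then fixed: "Our first model will include one observation per clinician and will include a random intercept for organization, but no independent variables". A second model adds the three assessments as fixed effects. The article reads this second model in two ways: as the individual contribution of each organizational factor, and as the part of the organizational variation in competency that the factors explain. It mentions no averaging of ratings to site level, no centring within site and no site-mean term.

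Elsewhere the article treats these factors as properties of the organization. In the text on organizational factors that follows Figure 1, readiness is a construct that "reflects how the sum of individual attitudes and behaviors operate at a collective level within an organization". Under Measurement, leaders, supervisors and direct care staff are all surveyed "because reliable assessment requires multiple perspectives". The instrument descriptions show that staff at one site rate the same object: the executive leadership, the working environment of the agency, and the agency as a whole.

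**The concern.** Colleagues at one site rate one agency, so differences between their ratings are differences in perception. Differences between organizations appear only between sites. A random site intercept does not separate the two when the rating enters as one uncentred, clinician-level fixed effect. The fitted coefficient is then a weighted average of a within-site slope and a between-site slope. The article names only the organizational interpretation, while the design puts most of the information within sites.

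At stake is the organizational guidance that Aim 2 is meant to give. The Conclusions section says that organizational factors will show under what conditions the intervention works and will inform later implementation research. A within-site perception effect could be reported as an organizational effect, and a real organizational effect could be missed. The Aim 1 effectiveness comparison is not affected.

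**Working it through.** **Inputs from the protocol article**
- Sites: Randomization gives "yielding 7 sites per condition, balanced by state", and Aim 2 uses intervention agencies only, so J = 7.
- Raters per site: Participants gives "five clinical supervisors, ten direct care staff and five leadership staff will be recruited to participate in the study". Supervisors plus direct care staff give n = 5 + 10 = 15. Quantitative Data analysis also says "The unit of observation in all models will be, as appropriate, clinical supervisors, organizational leaders or consumers", which omits direct care staff, so n = 5 (supervisors only) is tried as well.
- Outcome intracluster correlation (ICC): ICCy = 0.013, the pilot value under Participants. The variable it belongs to is not named.

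**Assumption**
- Site ICC of the ratings, ICCx: not in the document, varied from 0.05 to 0.30.

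The article gives no figure for the Aim 2 model itself, so there is none to reproduce. Its provider total does reproduce: 14 × 20 = 280.

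**Formulas** (expected generalized least squares weights, random-intercept model, uncentred predictor)
- Within-site information: W = J(n − 1)(1 − ICCx)
- Between-site information: B = (J − 1)(1 + (n − 1)ICCx)
- Discount on B: λ = (1 − ICCy) / ((1 − ICCy) + n·ICCy)
- Between-site share = λB / (λB + W)

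**n = 15.** λ = 0.987 / (0.987 + 0.195) = 0.835.

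| ICCx | B | W | λB | Between-site share |
|---|---|---|---|---|
| 0.05 | 10.2 | 93.1 | 8.52 | 8% |
| 0.10 | 14.4 | 88.2 | 12.02 | 12% |
| 0.20 | 22.8 | 78.4 | 19.04 | 20% |
| 0.30 | 31.2 | 68.6 | 26.05 | 28% |

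**n = 5.** λ = 0.987 / (0.987 + 0.065) = 0.938.

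| ICCx | B | W | λB | Between-site share |
|---|---|---|---|---|
| 0.05 | 7.2 | 26.6 | 6.76 | 20% |
| 0.10 | 8.4 | 25.2 | 7.88 | 24% |
| 0.20 | 10.8 | 22.4 | 10.13 | 31% |
| 0.30 | 13.2 | 19.6 | 12.38 | 39% |

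**Break-even.** Setting λB = W gives ICCx of about 0.55 for n = 15 and 0.44 for n = 5.

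**Sensitivity to ICCy.** At an assumed ICCy of 0.10, the shares over the same ICCx range fall to 4% to 15% (n = 15) and 15% to 30% (n = 5). A larger outcome ICC makes the problem worse.

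**Simulation check.** REML fits of the three-predictor model, 7 sites, ICCy = 0.013, 600 runs per setting. The true slope of 0.4 is placed at one level only.

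| n | ICCx | Level of true slope | Mean estimate | Significant |
|---|---|---|---|---|
| 15 | 0.10 | within only | 0.37 | 94% |
| 15 | 0.10 | between only | 0.02 | about 5% |
| 15 | 0.30 | within only | 0.33 | 86% |
| 15 | 0.30 | between only | 0.06 | 10% |
| 5 | 0.10 | within only | 0.38 | 53% |
| 5 | 0.10 | between only | 0.03 | 7% |

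With no organizational effect at all, the coefficient usually appears in full. With a real organizational effect and no perception effect, it nearly vanishes.

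**The case against.** **The article does not say outright that ratings stay at clinician level.** One row per clinician is compatible with site-mean predictors, and the need for several perspectives could point to pooling. In the later consumer-outcome models no link from clinician to consumer is described, so some aggregation would probably be needed there. This limits the point to the clinician competency model. There, the article names the predictors, the row unit and the model, and the plain reading is a clinician-level rating in a clinician-level model.

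**The sentence that fixes the layout describes a model without predictors, which is standard.** That is right. The fault arises in the second model, together with the definition of the independent variables.

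**Part of the stated question is about perception.** The Abstract and the Aim 2 text ask how far clinicians' assessments are associated with competency, and the model answers that. What it does not support is the further reading as organizational contribution and organizational variation explained.

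**Aim 2 is associational, and the Mixed methods section already concedes possible lack of power for implementation outcomes.** Both are true, but low power is a different matter from a coefficient that estimates something else.

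**Stronger readings the document does not support.** A reader might infer that the within-site part must dominate. That depends on the ICC of the ratings, which is not given. A reader might also infer confounding by staff role, because of the supervisors' additional contact ("The second monthly call will involve the clinical supervisors only"). That call bears on competency and gives no reason for supervisors to rate the agency differently. The article also plans separate models by data source, with a unit of observation that omits direct care staff, so the two roles may never be pooled. No false-positive rate for role confounding can be derived from the document, and no role or state term is requested here.

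**Conclusion.** The concern holds in conditional form. As written, the second Aim 2 model gives one coefficient per factor that mixes perception within sites with differences between sites, and labels it organizational. At ICCy = 0.013 and assumed rating ICCs of 0.05 to 0.30, 72% to 92% of the weight is within-site with 15 clinicians per site, and 61% to 80% with 5 supervisors per site. The majority reverses only above a rating ICC of about 0.55 or 0.44 respectively. These figures rest on 7 equal-sized sites, on the pilot ICC applying to competency change, and on ratings entering without aggregation. Nothing in the document shows that the two slopes do differ. The defect is that the model cannot tell them apart.

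**What to change.** For the clinician competency model, replace each factor by two terms: the site mean of staff ratings, and the clinician's deviation from that mean. Keep the leaders' self-ratings out of the site mean and report them separately, because on the leadership questionnaire leaders rate themselves while staff rate the leaders. Interpret only the site-mean coefficient as organizational, and report the deviation coefficient as individual perception.

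Enter the factors one at a time and label the organizational results exploratory. Three site means plus an intercept on 7 sites leave 7 − 4 = 3 residual degrees of freedom. The critical t is 3.18, so a partial correlation would have to exceed 3.18/√(3.18² + 3) = 0.88 for two-sided p < 0.05. One site mean plus an intercept leaves 5 degrees of freedom (t = 2.57) and a threshold of 2.57/√(2.57² + 5) = 0.75, which is still demanding.

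The cost is analysis wording only, with no new data. The downside is that the organizational coefficients will have very wide intervals, and entering factors singly gives up mutual adjustment. The limit of 7 sites already exists in the design; the current model hides it.
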